**FIGURE 1 F1:**
[figure not shown]
Flowchart of the VENUS registry. Abbreviations: IS, ischemic stroke; NC, Naoshuantong capsules.

### Study population

In order to achieve a high population representation, we registered patients with a unstrict inclusion criterion. All adult patients (≥18 years) admitted to the participating sites with a clear diagnosis of IS according to the guideline were screened. Patients who were newly treated with NC within 30 days of symptom onset were consecutively included in this study. Patients with other complications that hinder the assessment of neurological function and disability will be excluded. Patient participation is entirely voluntary and written informed consent that complies with the Declaration of Helsinki principle will be obtained from all patients or their legally authorized representatives.

### Data collection and management

The research personnel who are appointed at each participating site will be responsible for data collection. They will consecutively screen eligible patients and then record data using paper-based registry forms (PRF). Baseline data including patients’ demographics, past medical history, physical examination, laboratory test and auxiliary examination results, risk factor assessment, and the medical combination will be abstracted from the medical records. The symptom classification of IS will be judged based on the Oxfordshire Community Stroke Project (OCSP) criteria, and the etiological classification will be determined according to the Trial of Org 10172 in Acute Stroke Treatment (TOAST) criteria (Bamford et al., 1991; Adams et al., 1993). At baseline, the life dependency will be measured with the modified Rankin Scale (mRS), the neurological impairment will be measured with the National Institute of Health Stroke Scale (NIHSS), the activity of daily living will be measured with the Barthel Index (BI), the cognitive function will be measured with the Mini-Mental State Examination (MMSE), and the Chinese medicine syndrome will be measured with the Diagnostic Scale of Syndrome Elements in Ischemic Stroke (DSSEIS) (Folstein et al., 1975; Kasner, 2006; Gao et al., 2011; Gao et al., 2012). Additionally, the NC prescription details (dosage and frequency) and clinical physicians’ prescriptionology information will also be documented. The blood samples will be collected from 40 patients eligible from Dongzhimen Hospital and Xuanwu Hospital, Beijing, China. An independent data safety and monitoring board will conduct data monitoring to ensure adherence to study documentation, reporting procedures, and the study protocol.

### Follow-up procedures

The research personnel will regularly perform face-to-face or telephone follow-ups at 2, 4, 8, and 12 weeks after the initial patient registry, and 180 days after IS onset. Information including death, recurrent stroke events, and adverse events will be obtained during the whole study. Details of the follow-up timetable on life dependency, neurological impairment, activities of daily living, cognitive functions, and Chinese medicine syndrome collection are as follows: 1) assessment of mRS will be conducted at all follow-up time points mentioned previously; 2) assessment of DSSEIS, NIHSS, and MMSE will be conducted at 2, 4, 8, and 12 weeks after patient registry; 3) assessment of BI will be conducted at 2, 4, and 8 weeks after patient registry. The aforementioned blood samples will be collected again from 40 patients, at 4 weeks after patient registry. Adherence to the NC treatment and medicine combination will be recorded at 2, 4, 8, and 12 weeks after patient registry. The results will be recorded if the patients receive examination with regard to laboratory tests, magnetic resonance imaging (MRI) or computed tomography (CT), and transcranial Doppler sonography. Death will be confirmed by a death certificate. Recurrent stroke events leading to rehospitalization will be confirmed by discharge diagnosis while suspected recurrent stroke events will be determined by the endpoint judgment committee when without hospitalization (Feng et al., 2021). Adherence to the NC treatment will be defined as the proportion of prescribed doses taken (Osterberg and Blaschke, 2005).

### Study outcomes

The primary outcomes of the VENUS registry is the changes of life dependency measured with the distribution of scores on the mRS at 12 weeks after initial patient registry. The secondary outcomes are measured with different indicators those will be assessed at subsequent follow-up visits, such as changes in neurological impairment, long-term safety, improvements in neurological function, improved activities of daily living, favorable functional status, changes in cognitive functions, all-cause mortality, recurrent stroke events, and adherence to NC treatment. In addition, we will exploratively detect the biological outcomes by using the RayBiotech human inflammatory factor antibody array Q3 (RayBiotech, Inc., QAH-INF-3-1) to profile the variations of the inflammatory indicators in the blood samples. The detailed study outcomes of the VENUS registry are illustrated in Table 1.

**TABLE 1 T1:** Complete outcomes of the VENUS registry.

Primary outcome
Distribution of scores on mRS at 12-week follow-up
Secondary outcome
Change in the NIHSS score between baseline and 4-week follow-up
Recurrent stroke events (ischemic stroke, hemorrhagic stroke which includes intracerebral hemorrhage and subarachnoid hemorrhage) within 2-week, 4-week, 8-week, 12-week, and 180-day follow-up
Composite end points of recurrent stroke events and death within 2-week, 4-week, 8-week, 12-week, and 180-day follow-up
Proportion of patients with an mRS score ≤2 at 2-week, 4-week, 8-week, 12-week, and 180-day follow-up
Distribution of scores on mRS at 2-week, 4-week, 8-week, and 180-day follow-up
Proportion of patients with the BI score ≥90 at 2-week, 4-week, 8-week, 12-week, and 180-day follow-up
Change in the NIHSS score between baseline and 2-week, baseline and 8-week, baseline and 12-week, baseline and 180-day follow-up
Proportion of patients with the BI score ≥90 at 4-week and 180-day follow-up
NC treatment duration within 2-week, 4-week, 8-week, 12-week, and 180-day follow-up
MMSE scale score at 2-week, 4-week, 8-week, 12-week, and 180-day follow up
All-cause mortality within 12-week and 180-day follow-up
Incidence of adverse events during the whole study
Exploratory outcome
^a^Variation of inflammatory indicators between baseline and 4-week follow-up

Abbreviations: mRS, modified Rankin scale; NIHSS, National Institute of Health Stroke Scale; BI, Barthel Index; MMSE, Mini-Mental State Examination; NC, Naoshuantong capsules.

a The inflammatory indicators include BLC, Eotaxin-1, Eotaxin-2, GCSF, I-309, ICAM-1, IFN-γ, IF-1 α, IL-1ra, IL-2, IL-4, IL-5, IL-6R, IL-7, IL-8, IL-10, IL-12 p40, IL-12 p70, IL-13, IL-15, IL-17A, MCP-1, M-CSF, MIG, MIP-1 β, MIP-1 δ, PDGF-BB, RANTES, TIMP-2, TNF-α, TNF-β, and TNF RI.

### Study sites and data source

The VENUS registry steering committee will screen the ranks of hospitals in different regions of the Chinese mainland, and then evaluates their research capability and commitment to the registry with preliminary surveys. After balancing the geographical representation and research capability of the hospitals, only those hospitals that are equipped with MRI or CT machines, having experience in multicenter studies, and that can totally grasp research requirements are finally selected as participating sites of the VENUS registry. The geographical distribution of the selected 84 participating sites is shown in Figure 2.

**FIGURE 2 F2:**
[figure not shown]
Sites distribution of the VENUS registry.

### Quality control and management

All research personnel who participate in this study receive specific training in accordance with the protocol, processes, and details of the VENUS registry. An independent contract research organization will check for the completeness and accuracy of internal logic and the medical reference range of the PRF during the study. Any correction made on the PRF will be left with a signature and accurate date. Once the PRF is audited and approved, two research personnel will conduct back-to-back data entries into an electronic data capture system which can automatically check the completeness, accuracy, and consistency of the double-entry data, and then warn the researcher if any error or query exists. Afterward, the research personnel will check the original data and then gives feedback.

### Study sample size

Similar to other large-scale, high-quality registry studies, formal hypotheses for sample size estimation are deficient in the VENUS registry (Lei et al., 2020; Gardner et al., 2021). As a general rule, the sample size of the registry is supposed to be sufficient enough to represent the general population. Based on the crude incidence of IS in China, we planned to register 5,000 patients with IS in the VENUS registry.

### Statistical analysis

All data will be summarized as means and standard deviations for normally distributed continuous variables, while the median and interquartile range will be calculated for non-normally distributed continuous variables, and will be presented as counts and percentages for categorical variables. Comparisons will be made using parametric tests [one-way analysis of variance (ANOVA) or t-test], or nonparametric tests (chi-square test, Fisher’s exact test, Kruskal–Wallis one-way ANOVA on ranks, or Mann–Whitney *U* test) as appropriate. Multivariable regressions will be conducted with adjustments for potential covariates and the propensity score matching method will be used to minimize the influence of the other potentially unbalanced variables. Time-to-event outcomes will be presented using Kaplan–Meier methods and hazard ratios and the corresponding 95% confidence intervals will be derived from the Cox proportional hazards regression models, and the treatment effect will be assessed using the log-rank test.

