The global spread of the COVID-19 outbreak has presented huge challenges for public health and for conducting clinical research in terms of patient compliance and follow-up; therefore, patient enrollment is slightly delayed when compared to the anticipated completion time to ensure continuity, completeness, and accuracy of the data. As such, 4,981 patients have been enrolled in the study, of which 4,185 have been included in the final analysis. The study profile and baseline characteristics of the patients were reported. According to the current data analyses, VENUS and CNSR-III have a similar severity distribution of neurological deficits evaluated by NIHSS (Wang et al., 2019). Compared to previous national stroke registries, the VENUS registry is exclusive as it allows for the evaluation of evolution of syndrome elements at different time points of IS, which contributes to targeted, personalized precision therapy for IS based on syndrome differentiation. Moreover, the VENUS registry is closer to clinical practice in the real-world setting than rigorous RCTs. According to the current statistical analysis of baseline information, the internal-wind element comprises the largest proportion, which could be rationally explained by 93.73% of patients in the acute phase of IS and is consistent with the findings of previous studies (Xin et al., 2016). Similar to other observational registry studies, selective biases in the VENUS registry are unavoidable although the targeted sample population covers a relatively larger number of regions in the Chinese mainland (Ohman et al., 2006; Venketasubramanian et al., 2015). However, cross-sectional and longitudinal data from the multicenter participation and regular sequential follow-ups of registered patients are planned, and both the geographical and temporal characteristics of patients with IS can be explored to improve the representation of the study findings. Furthermore, special populations (such as elderly patients or patients with severe comorbidities) who are normally excluded from clinical trials will be registered based on the unstrict inclusion criteria of this registry, increasing the generalizability of the results in real-world settings. Strict quality control in terms of research personnel training and timely audits will be conducted before study initiation to ensure the accuracy and completeness of the collected data. In addition, the VENUS registry will support the establishment of a database for further individual patient data pooling as per homogenous investigational variables with that of the China Stroke Registry for Patients with Traditional Chinese Medicine (CASES-TCM) study, embedding comparative effectiveness research, pragmatic randomized clinical trial, or nested case–control study to generate secondary hypotheses for extra validation in clinical trials (Feng et al., 2021).

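### Recurrent stroke falls under a general Kaplan-Meier sentence; with deaths censored its absolute risk is slightly overstated, and cumulative incidence would be the better presentation (minor)

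*Protocol article*

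**What the plan says.** The Statistical analysis section gives one approach for event times: "Time-to-event outcomes will be presented using Kaplan–Meier methods", followed by Cox hazard ratios with 95% confidence intervals, and "the treatment effect will be assessed using the log-rank test". It does not say which outcomes are analysed this way, and it mentions neither competing risks nor cumulative incidence.

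Table 1 under Study outcomes lists three clinical event outcomes over fixed windows:

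- "Recurrent stroke events (ischemic stroke, hemorrhagic stroke which includes intracerebral hemorrhage and subarachnoid hemorrhage) within 2-week, 4-week, 8-week, 12-week, and 180-day follow-up"
- a composite that counts either a recurrence or a death, over the same five windows
- "All-cause mortality within 12-week and 180-day follow-up"

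In the second and third, death is itself an event. In the first it is not.

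The data that separate these outcomes are collected. Follow-up procedures states: "Information including death, recurrent stroke events, and adverse events will be obtained during the whole study".

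**The concern.** A patient who dies without a recurrence can no longer have one. Kaplan-Meier applied to recurrence alone treats that patient as censored, as if still at risk after death. One minus the curve then estimates recurrence risk in a setting where nobody dies first, which is higher than the share of registered patients who recur. A descriptive registry would normally want that share.

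The overstatement grows with the death rate, so it is not the same in every cohort. The first aim under Study design is to look for differences in effectiveness between groups of users with different clinical profiles. If absolute recurrence risks are read off Kaplan-Meier curves and set side by side, part of what is seen, or not seen, can come from differing mortality.

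**Working it through.** **Inputs from the article.** Kaplan-Meier is the only estimator named for event times. Recurrent stroke is listed without death. Follow-up ends 180 days after onset. 4,185 patients enter the analysis, of whom 51.62% have an NIHSS of 0–3 and 72 (1.72%) are in the highest NIHSS band (Table 2).

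**Inputs that are assumed.** The article gives no recurrence or death rate, overall or by group, and no figure on this point to reproduce. All rates below are assumptions, shown as a range.

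**Formula.** Let R be the 180-day recurrence risk read from one minus Kaplan-Meier with deaths censored, and D the corresponding figure for death. With constant cause-specific hazards over the period,

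- h1 = −ln(1 − R) and h2 = −ln(1 − D)
- cumulative incidence of recurrence: CIF = h1/(h1 + h2) × [1 − exp(−(h1 + h2))]
- excess = R − CIF

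**One case in full.** R = 10%, D = 20%: h1 = 0.1054, h2 = 0.2231, sum 0.3285. The bracket is 1 − 0.90 × 0.80 = 0.28. CIF = (0.1054/0.3285) × 0.28 = 8.98%. The excess is 1.02 points, or 11.4% relative to the CIF.

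**Range.**

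| R (1 − KM) | D | CIF | Excess, points | Relative |
|---|---|---|---|---|
| 5% | 1% | 4.98% | 0.02 | 0.5% |
| 5% | 5% | 4.88% | 0.12 | 2.6% |
| 8% | 5% | 7.80% | 0.20 | 2.6% |
| 10% | 10% | 9.50% | 0.50 | 5.3% |
| 10% | 20% | 8.98% | 1.02 | 11.4% |
| 10% | 30% | 8.44% | 1.56 | 18.5% |

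**Sensitivity to timing.** If both hazards are front-loaded in the same way (Weibull shape 0.5), the results do not change. If only one is front-loaded, the last row ranges from 1.04 points (recurrence early) to 2.07 points (death early), or 11.7% to 26.1% relative.

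**Against sampling error.** At 5% recurrence and n = 4,185 the 95% half-width is 1.96 × √(0.05 × 0.95/4185) = 0.66 points, well above the whole-cohort excess of 0.02–0.12 points at that recurrence level. At 10% recurrence in the 72 patients of the highest NIHSS band it is 1.96 × √(0.10 × 0.90/72) = 6.9 points, again above the excess.

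**Effect on a comparison of two cohorts.** The direction is not fixed:

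- R = 10% in both, D = 5% and 20%: Kaplan-Meier shows no difference; the CIFs are 9.75% and 8.98%.
- R = 8% with D = 5%, against R = 10% with D = 30%: Kaplan-Meier differs by 2.0 points, the CIFs (7.80% and 8.44%) by 0.64.
- R = 10% with D = 5%, against R = 8% with D = 30%: Kaplan-Meier differs by 2.0 points, the CIFs (9.75% and 6.75%) by 3.0.

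**Consistency with Table 1.** Cumulative incidence of recurrence plus that of death without prior recurrence equals the composite. With R = 10% and D = 20% this is 8.98% + 19.02% = 28.0%. The two Kaplan-Meier figures sum to 30%.

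**The case against.** The strongest reply is that this is detail for an analysis plan. The article covers all analyses in a few sentences and ties no outcome to a method, and the analysis plan, which may well handle competing risks, is not shown. Recurrent stroke could also be reported as a simple percentage within each window; with complete follow-up that percentage is already the share who recur. The composite and all-cause mortality are listed as well, so a reader can see whether deaths matter. This justifies a low rating. It does not remove the point, because the article does state a method for event-time outcomes, without exception, and recurrent stroke within a window is a natural member of that class.

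A second reply stands in full: Cox hazard ratios and log-rank tests with deaths censored are valid for the cause-specific hazard of recurrence. Only the absolute risk curves are at issue. Gray's test answers a different question and is not a correction of the log-rank test.

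Three stronger readings might be inferred, and the documents do not support them:

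- *That Kaplan-Meier is wrong throughout.* It is appropriate for all-cause death and for the composite.
- *That the registry plans to compare elderly or severe patients and will overstate recurrence most there.* The Discussion says "special populations (such as elderly patients or patients with severe comorbidities) who are normally excluded from clinical trials will be registered", but in support of generalizability, and the adjective describes comorbidities, not stroke severity. The first aim names neither group. Higher mortality in them is a reasonable assumption, not a reported figure.
- *That the method creates or enlarges group differences.* The examples above show that it can enlarge, shrink or hide them.

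**Conclusion.** The point holds as a minor one. If recurrent stroke is presented under the general sentence with deaths censored, its absolute risk is overstated whenever patients die without a recurrence; the direction of that error is certain. Its size depends on assumed rates and roughly constant hazards: about 0.02–0.2 points for 5–8% recurrence with 1–5% deaths, and 1.0–1.6 points for 10% recurrence with 20–30% deaths. In a registry where about half the patients have mild strokes and follow-up is 180 days, the overall effect is likely to be negligible and below sampling error. It becomes noticeable only in a cohort with high mortality. Unlike sampling error, it does not shrink with more patients, and it can distort absolute comparisons between cohorts with different mortality. The planned hazard ratios and tests are not invalidated.

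**What to change.** Add a sentence to the analysis plan, and to the article if it is revised:

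- Present recurrent stroke as cumulative incidence (Aalen-Johansen) with death without prior recurrence as the competing event, at the five windows of Table 1.
- Keep the planned Cox and log-rank analyses for recurrence, and label the results cause-specific.
- Keep Kaplan-Meier for all-cause death and for the composite of recurrence and death.
- Gray's test may be added if a comparison of the incidence curves themselves is wanted; it is optional.

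The cost is that sentence and standard software. Deaths and recurrences are already recorded throughout, so no new data are needed. If no one is lost to follow-up, the estimate reduces to the crude percentage, so nothing is given up.

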## Result

The study is currently ongoing, and the data are continuing to be collected. A total of 4,981 eligible patients with IS have already been enrolled from April 2019 to July 2021 in 84 participating sites. There are currently 4,185 patients entering into statistical analysis after excluding 266 patients with missing baseline information, 297 patients with non-IS diagnosis, 172 patients who lacked imaging data collected upon stroke onset, 21 patients who refused follow-up, and 40 patients with incorrect medication information. The detailed patient enrollment flow chart is shown in Figure 3.

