## Abstract

**Background:** Naoshuantong capsules (NC) are commonly used for the treatment of ischemic stroke. Experimental research and small-sample clinical trials have demonstrated that NC is effective in improving neurological recovery. Yet, there is a substantial lack of high-quality evidence on the precision treatment population of NC and long-term safety when making real-world clinical decisions. The acquisition of prospective longitudinal data in the real-world setting is essential to fully characterize the effectiveness and safety profile of NC for patients with ischemic stroke.

**Methods:** The Vital real-world Experience regarding Naoshuantong capsules for Unselected ischemic Stroke (VENUS) registry is a prospective, multicenter, observational study aiming to register 5,000 patients. Eligible adult patients diagnosed with ischemic stroke and newly treated with NC within 30 days of symptom onset will be consecutively registered from 84 participating sites across the Chinese mainland. Baseline data will be recorded at the patient registry, and all patients will be regularly followed up at 2, 4, 8, and 12 weeks after the initial patient registry, and 180 days after ischemic stroke onset. The primary outcome is the distribution of scores on the modified Rankin Scale at 12 weeks after initial patient registry. Adverse events will be recorded during the study for NC safety assessment.

**Results:** A total of 4,185 patients with ischemic stroke were enrolled, among which 37.06% patients were female. The average age of all patients was 65.22 years. The proportion of patients whose course of ischemic stroke was less than 14 days accounted for 93.45%.

**Conclusion:** The VENUS registry is designed to comprehensively document medical data regarding NC treatment for ischemic stroke in real-world settings. The findings of this study will provide valuable insights into the clinical management of patients with ischemic stroke and the subsequent outcomes of the use of NC when included in the best clinical practice.

Study registration: This study was registered with the Chinese Clinical Trial Registry (URL: http://www.chictr.org.cn/index.aspx, Unique identifier: ChiCTR1900025053).

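### After enrolment, 499 of 4,684 patients not removed as non-IS (10.7%) are dropped from the set called final, for reasons that are not stated exclusion criteria; the enrolment counts also conflict

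*Protocol article*

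**What the plan says.** The Result section reports enrolment as "A total of 4,981 eligible patients with IS have already been enrolled from April 2019 to July 2021 in 84 participating sites". It continues: "There are currently 4,185 patients entering into statistical analysis after excluding 266 patients with missing baseline information", then "297 patients with non-IS diagnosis", then "172 patients who lacked imaging data collected upon stroke onset, 21 patients who refused follow-up, and 40 patients with incorrect medication information". The same section says that the study is still running. The Discussion nevertheless states "4,981 patients have been enrolled in the study, of which 4,185 have been included in the final analysis". The abstract gives a different enrolment figure: "A total of 4,185 patients with ischemic stroke were enrolled".

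Study population asks for adults with a clear guideline diagnosis of IS who were newly treated with NC within 30 days of onset, included consecutively. Its one exclusion is complications that prevent assessment of neurological function and disability.

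Study outcomes makes the 12-week mRS distribution primary and lists "Incidence of adverse events during the whole study" among the secondary outcomes. Long-term safety is one of the specific aims under Study design. Statistical analysis plans Kaplan–Meier and Cox methods for time-to-event outcomes.

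**The concern.** The article does more here than leave a detail to another document. It states who was removed after enrolment and labels the remainder as the final analysis.

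Three of the reasons concern the record rather than the patient's eligibility as written: baseline information, imaging and medication information. The fourth, refusing follow-up, happens after enrolment. Deleting such patients tends to keep the well-documented and cooperative ones. That sits badly with a registry that calls its population unselected, enrols consecutively and claims generalizability to elderly and severely comorbid patients.

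Two results are at stake. One is the primary mRS distribution, together with the recurrence and mortality rates. The other is the adverse event incidence, because a patient who took NC remains exposed even if a baseline form or scan is missing.

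**Working it through.** **Inputs** (Result section): enrolled 4,981; removed for missing baseline information 266, non-IS diagnosis 297, no onset imaging 172, refused follow-up 21, incorrect medication information 40.

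**Reproducing the article's figure**
- 266 + 297 + 172 + 21 + 40 = 796
- 4,981 − 796 = 4,185, as stated
- 4,185/4,981 = 84.0% kept and 796/4,981 = 16.0% removed

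**Separating the non-IS patients**
- 4,981 − 297 = 4,684 not removed as non-IS
- 266 + 172 + 21 + 40 = 499 removed for the other four reasons
- 499/4,684 = 10.7% removed and 4,185/4,684 = 89.3% kept

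**If some of the 499 are really ineligible**
- All 172 without imaging set aside: (499 − 172)/(4,684 − 172) = 327/4,512 = 7.2%
- The 40 with incorrect medication information set aside as well: 287/4,472 = 6.4%

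**Is the 4,185 a complete-record set?** In Table 2 the categories of BMI (114 + 1,947 + 1,758 + 366), mRS (1,754 + 1,152 + 1,279) and BI (2,377 + 1,808) each total 4,185. So do those for education, insurance, TOAST, smoking and NIHSS. No patient in the set lacks any of these items.

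**Illustration only.** The article reports no outcome rates, so every rate below is assumed.
- mRS ≤2 at 12 weeks assumed to be 80% in the 4,185, that is 3,348 patients. The sampling half-width is 1.96 × √(0.8 × 0.2/4,185) = 1.2 points.
- If the 499 do 10 or 20 points worse, the rate over 4,684 is (3,348 + 499 × 0.70)/4,684 = 78.9% or (3,348 + 499 × 0.60)/4,684 = 77.9%. If they do 10 points better, it is 81.1%.
- The extreme bounds are 3,348/4,684 = 71.5% (none of the 499 reach mRS ≤2) and 3,847/4,684 = 82.1% (all do).
- Adverse events assumed to be 5% in the 4,185, and 0.5, 2 or 3 times that in the 796, with all 796 taken as exposed: (0.05 × 4,185 + 0.05 × k × 796)/4,981 = 4.60%, 5.80% or 6.60% for k = 0.5, 2 and 3.

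The sign changes with the assumption. A 10-point difference in the 499 moves the mRS proportion by 1.1 points, about the size of the sampling error; a 20-point difference moves it by 2.1 points.

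**Counts set side by side.** The abstract has 4,185 enrolled, whereas the Result and Discussion sections have 4,981. The Result section describes all 4,981 as eligible with IS, and then removes 297 because they did not have it.

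**The case against.** A reader might infer that effectiveness rests on a selected 84% of patients, that adverse events among 796 patients are lost, that the bias flatters NC, and that the plan has no safety set. The documents do not support these readings.

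- **The 84%.** It counts the 297 non-IS patients, whose removal from effectiveness follows the entry criterion. For effectiveness the retained share is 89.3%. The 84.0% fits only a safety denominator, and only if everyone enrolled took NC.
- **Lost adverse events.** No section ties an adverse event rate to the 4,185; only baseline characteristics are shown for that set. Follow-up procedures collects deaths, recurrences and adverse events throughout, without limiting this to the 4,185.
- **No safety set.** A condensed article commonly leaves analysis populations and imputation methods to the full protocol or SAP, which are not shown. Their absence here is not a finding.
- **Eligibility.** Some of the 172 without imaging may have unconfirmed IS, and some of the 40 may not have been newly treated with NC. The article does not say.
- **Direction and size.** Both depend on assumed rates. The extreme lower bound needs all 499 to finish above mRS 2, although (1,754 + 1,152)/4,185 = 69.4% of the analysed patients were at mRS ≤2 at baseline.
- **Admitted limits.** The Discussion itself concedes that selection bias is unavoidable, and it calls the analysis final although the study is described as ongoing.

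All of this stands, and it narrows the point. It does not remove it. Even with all 172 and all 40 treated as ineligible, 287 of 4,472 patients (6.4%) are dropped for missing baseline information or refused follow-up. The conflicts over enrolment numbers do not depend on any unseen document.

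**Conclusion.** The point holds in a limited form. The article fixes a final analysis set that leaves out 499 of the 4,684 patients not removed as non-IS (10.7%), for reasons that Study population does not list as exclusions. Refusing follow-up is a post-enrolment event, and the planned Kaplan–Meier and Cox methods can deal with it by censoring.

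The omission can bias the mRS distribution and the event rates, but neither direction nor amount can be read from the article. The 10.7% treats all 4,684 as having IS and being newly treated with NC; it falls towards 6.4% if the 172 and the 40 all prove ineligible. Exposure to NC is implied by the entry criteria but cannot be confirmed for the 40.

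Separately, the abstract contradicts the Result and Discussion sections on the number enrolled, and the description of all 4,981 as eligible with IS contradicts the 297 later removed.

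**What to change.** 1. **Effectiveness.** Make the main set all enrolled patients with IS who were newly treated with NC. Exclude only the 297 non-IS patients and any of the 172 or 40 shown, with the reason recorded, to fail an entry criterion.
2. **Refusers and missing data.** Censor the 21 refusers at last contact in time-to-event analyses. Handle missing baseline and outcome data, including 12-week mRS, by multiple imputation where the available data allow. This has limits, because 266 of the 499 lack baseline information to an unstated extent.
3. **Sensitivity.** Keep the 4,185 as a sensitivity analysis, and tabulate the available baseline data for excluded against retained patients.
4. **Safety.** State that adverse events are counted over every enrolled patient known to have taken NC, including non-IS patients (up to 4,981). If an unseen document already says so, a reference to it is enough.
5. **Counts.** Correct the abstract to 4,981 enrolled and 4,185 in the present analysis set, and reword the Result section so that the 297 are not first described as eligible with IS.
6. **Reporting.** Give any size of bias only as an illustration under stated assumptions.

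The cost is analysis-set wording, one imputation model and one extra table, with intervals that may be somewhat wider. No further patients are needed, and the article reports no outcome results yet.
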